#### MoB In-Person Intervention

A textbook explaining the detailed, step-by-step process and the techniques of the experimental educational method of the MoB in-person education has been devised. According to the data acquired in Stage 1, the MoB in-person intervention comprises a total of 12 in-person educational sessions, with one session per week. Each session has a duration of 1.5 hours and the maximum number of participants in the groups is 12 patients.

#### MoB Digital Platform

The interactive part of the platform is under development, while the informative part is live [52] and accessible to the participants in the current study, as well as to any interested person (eg, family members of people with BP) or caregivers providing updated information related to BD (platform users). The platform is in the form of a dynamic website with user-generated content as well as static information, following a responsive design (ie, accessible with all types of devices). The informative part, so far, includes the following functionalities: self-management action plan, homework exercises, self-assessment tools, and scientific articles relevant to BD. Entry into the platform functionalities (scientific articles excluded) is password-protected.

Users can register in the platform by filling in their personal profile and can log out/log in and revisit at their convenience. Regarding self-management functionalities, the platform will contain subject units where personal relapse symptoms may be registered, a life events table, personal risk factors for relapse, and a weekly program of activities. Input of relevant information will be provided through open-ended questions and checklists. Participants of the MoB in-person intervention who visit the platform will find that these subject units (chapters) are topics on which they will be educated on. Additional features will be incorporated according to development of Stage 1 (eg, new training needs as described by participants in the focus groups).

Another subject unit will be the personal therapy file, where users will have the chance to keep tabulated notes related to their therapy, including information about the dose and type of medication treatment, as well as pending medical tests (eg, blood tests) and other relevant information. The therapeutic team of the user will have the ability to access the information by registering in the platform under approval of the user with the aim to support continuity and share information.

### Stage 3

The recruitment of the participants of the intervention group (40 patients) and the control group (40 patients) began during the first semester of 2021.

### Stage 4

User behavior data have been analyzed through Google Analytics by tracking the platform for approximately 1.5 years (January 2019 to October 2020). Specifically, we have recorded that 2180 users have visited the platform with an average session duration of almost 2 minutes. The bounce rate of these visits is 68%, which calls for improvement. The returning visitor rate is approximately 10%, and 70% of the visitors are accessing the platform via mobile and tablet devices.

The website has a total of 7100 page views. Each user has an average of 2.6 pages per visit. In terms of search appearance, it seems that 72% of the traffic is derived from organic searches, which means that search engine optimization fundamentals have been applied to the highest level. Usability testing is being performed to ensure that the website is improving the lives of the users.

The full development and release of the interactive part of the digital platform is expected to be finalized by the second semester of 2022, at which time the assessment of the applicability of the platform will take place.

The timeline of the proposed study is presented in Figure 1.

**Figure 1 figure1:**
[figure not shown]
Timeline of the Management of my Bipolarity (MoB) study. BD: bipolar disorder.

### Confidentiality and Dissemination

#### Ethics and Data Management

Participation in all stages of the study will follow the provision of informed consent. The participants will be informed both orally and in written form about the purpose and process of the study, as well as about confidentiality issues regarding the revealed experiences and the safe storage of the collected data. The principal investigator (AH) will answer all questions. The consent form will include a telephone number and email address for expressing complaints relating to the procedures of the study. Participants will be able to withdraw at any point as they wish, with no repercussions in the therapeutic procedure they already follow.

Each interview will be recorded with the participant’s permission. Moreover, the participants will be reassured that no data that could reveal their real identity would be presented or reported at any point of the study. Pseudonyms will be used for participation in the study. Although there is no identified psychosocial or other type of danger or harm related to participation in this study, the research team will provide psychosocial supportive services to those in need during the study and for up to 1 year after its completion.

#### Dissemination Policy

Dissemination of the results will take place through publications in international and national scientific journals. There will also be presentations of the data in nursing and medical conferences at national and international levels. All publications and presentations that will be held will include the names of all the collaborators who contributed to the implementation of this study. The aim of the dissemination is to inform health professionals and researchers interested in the follow-up of similar methodological planning for intervention studies.

#### Data Management

The data collected from each participant will be encoded as a letter according to the group to which they will be assigned (ie, “I” for the intervention group or “C” for the control group) and the sequence number of entering this group (eg, I1 or C1). This algorithm is expected to produce a unique code for each participant. All data will be safely stored in a locked cabinet in the office of the main supervisor, MK. Access is granted only to MK and AH. The data will also be stored on the computer of the main supervisor. When the data are stored on the computer, AH and MK will perform a double check to assure that the questionnaires have been completed accurately. The data will be published immediately in scientific publications for their verification. Mechanisms to protect data, based on the General Data Protection Regulation, have been taken into account to ensure the security of sensitive information provided on the digital platform by its users. In relation to security of data linked to any kind of communication within the environment of the platform, the HTTPS encryption system will be applied. Moreover, in relation to privacy issues, a cookies system will be applied. Access to personal files will be password-protected and all relevant information will be encrypted. Identification issues will also be taken into consideration. Overall, further investigation on security, privacy, and identification issues will be ongoing.

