### Settings and Sampling

The target population is adults diagnosed with BD who are under treatment. The recruitment will be implemented in collaboration with the mental health services used by the participants. Specifically, both private and public mental health services in Cyprus have been informed about the objectives and procedures of the study through a specific communication process. Through this process, several patients have already been referred to the research team by their psychiatrists/therapeutic team coordinator to participate in Stage 1. As a result, convenience sampling will be combined with snowball sampling, according to study inclusion criteria set in every stage. The study is also posted on social media and groups related to BD (health care service users, health care professionals).

To promote participant retention, an action plan has been developed. Specifically, the principal investigator (AH) will arrange one or two social meetings with the participants of Stage 1 and Stage 3 to achieve some degree of intimacy, emphasize confidentiality, and ensure engagement with the study. The cost of these social meetings is covered by the Nursing Department of Cyprus University of Technology. Regarding the control group of Stage 3, the principal investigator (AH) will also make a phone call once or twice per month to reassure their participation in the study, as follows: “Hello, I am [name] from the MoB project. I’m calling to see how you are, and if you are still interested in participating in the project. The next appointment will be on date X. Is this okay with you, or do you have any other arrangements for the day?”

### Stage 1

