#### Intervention Procedure

The form of this intervention will be in groups or in person according to the participant’s choice (similar to the data collection process as detailed above). Additionally, all participants of this group will have access to the MoB digital platform and will be assessed via a checklist on the frequency and extent to which they use the digital platform in each in-person session.

The implementation methodology of the MoB in-person intervention will include videos and PowerPoint presentations, as well as interactive learning methods such as role playing, empowerment exercises, and live discussions.

The MoB in-person intervention will comprise a total of 12 educational sessions. Each session will have a duration of 1.5 hours and the maximum number of participants in the groups will be 12 patients. At the beginning of each session, the participants will be given the opportunity to record their feedback for the previous session and the impact of the training intervention so far for themselves and for their families/significant others. The intervention will be performed at Cyprus University of Technology and will be implemented by the principal investigator (AH). Participation in the educational intervention is free of charge. Moreover, there is no financial benefit for those participating in the study (participants, researchers) in terms of reimbursement or any other material benefit.

Those who wish to withdraw participation prior to completion of the intervention will be able to continue to receive information/knowledge about their illness through the digital platform.

The control (waiting) group will only have access to the MoB digital platform. Yet, it should be noted that the control (waiting) group will also receive the MoB in-person intervention if its effectiveness is shown at the end of the study. In this way, all participants will be given the chance to receive the MoB intervention.

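### Stage 3 participant codes contain the arm letter (I or C), which needlessly unmasks the main supervisor's data checks and the analysis

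*Protocol article*

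**What the plan says.** The Data Management section (under Confidentiality and Dissemination) fixes the coding rule. Data are "encoded as a letter according to the group to which they will be assigned", I for intervention and C for control, and the letter is followed by "the sequence number of entering this group (eg, I1 or C1"). The section adds: "This algorithm is expected to produce a unique code for each participant". It describes no neutral study number alongside this code.

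The same section restricts access to two people, the main supervisor and the principal investigator. Both "will perform a double check to assure that the questionnaires have been completed accurately".

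Two other sections bear on who already knows the arm. Under Intervention Procedure, the in-person programme "will be implemented by the principal investigator". Under Settings and Sampling, the same person "will also make a phone call once or twice per month to reassure their participation in the study", and these calls go to the control group.

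The Data Analysis section plans between-group comparisons by analysis of variance and t test, regression, and multiple imputation for missing data. It does not name the analyst.

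**The concern.** An identifier that contains the allocation reveals the arm on every coded form and data row. Masking of data checks and analysis is one of the few protections still open to a trial of face-to-face education, where participants and the session leader must know the arm. The coding rule gives that protection up.

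What is at stake is discretion after the answers are collected: which entries are queried, how a scale is scored, how missing values are imputed, and which outcome or model is put forward. Such decisions are safer when made without sight of the arm. The article leaves some of them open, so the exposure is not merely formal.

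**Working it through.** There is no figure of the plan's to reproduce and no effect size to compute. The check is to set the relevant sections side by side.

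**1. Does the code reveal the arm?** Yes. Under Data Management the first character is the group letter, and the letter plus sequence number is the unique code. No key is needed to read it.

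**2. Who handles coded data, and who would know the arm without the code?**

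| Role | Source | Arm known without the code? | Added exposure from the code |
|---|---|---|---|
| Principal investigator | Intervention Procedure; Settings and Sampling; Data Management | Yes: delivers sessions and calls controls | None |
| Main supervisor | Data Management (data checks, storage) | Not stated; no delivery role is described | Yes, if otherwise masked |
| Analyst | Data Analysis (role not named) | Not stated | Yes, if otherwise masked |

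Of the two people with access, one is unmasked whatever the label says. The loss that could be avoided lies with the supervisor and with whoever analyses the file.

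**3. Is there discretion for arm knowledge to act on?** Some.
- Effectiveness Evaluation lists seven outcome domains.
- The same section first defines impulse control by two items of the Young Mania Rating Scale (YMRS), aggressive behavior and sexual interest. It later defines it by the scale's total score. Someone must choose between these.
- Data Analysis names several methods and multiple imputation.

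A full protocol or analysis plan may settle these points. On the article's text, they would be settled by people who can read the arm from the identifier.

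**4. Which forms are affected?** Stage 3 plans 40 + 40 = 80 participants (Inclusion and Exclusion Criteria) and four evaluations (Effectiveness Evaluation), so 80 × 4 = 320 form sets. This assumes full recruitment and no missed visit. It counts labelled forms and does not measure bias. The Stage 4 platform questionnaires are anonymous and lie outside the count.

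**The case against.** The strongest reply is that the article nowhere claims blinding of assessors, checkers or analysts, so the code breaks no stated rule, and masked analysis is often specified in a fuller document. Both points are right. The concern is therefore not a contradiction and not a complaint about missing detail. It rests on a labelling rule that the article does state, and states badly.

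A reader might infer more than the text supports:

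- **That the label biases YMRS scoring.** The article does not say who rates the YMRS or that it is scored from coded sheets. If the principal investigator rates it, the arm is known regardless of the code. Who should assess is a separate question.
- **That baseline forms must be relabelled or completed with the arm known.** The code could be applied at filing or data entry, and the article does not place the first evaluation before or after allocation.
- **That every questionnaire in the study is affected.** Only Stage 3 forms are.
- **That the label distorts most outcomes.** Most are self-report sums, true-false percentages, or counts and days of hospitalization. Scoring is largely mechanical, and the label does not alter what participants answer. The described check concerns accurate completion, not adjudication.

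It is also fair to say that masking by A and B is fragile here. Platform-use checklists are described only for intervention sessions, and the discontinuation criteria are given only for the intervention group. Either record would reveal which arm is which if left in the dataset. This limits what a new code achieves alone, and the fix has to deal with it. The article does not show that the supervisor would otherwise be masked; that remains an assumption.

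**Conclusion.** The point holds in a limited form. The coding rule makes allocation readable to anyone handling coded Stage 3 data. It adds nothing to what the principal investigator already knows. It removes masking from the main supervisor's checks and from the analysis, where masking could otherwise have been kept.

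This rests on two assumptions: that the I/C code is the working identifier on forms and data rows, as Data Management implies, and that the supervisor and analyst have no other source of arm knowledge. The direction and size of any bias cannot be derived from the article, and the 320 form sets are only a ceiling on exposure. The point does not invalidate the design. It is a cheap improvement.

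**What to change.** Replace the I/C code with a neutral sequential ID, for example MoB-001, assigned at consent. Then:

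1. Hold the ID-to-arm list in a separate file. It should not sit on the supervisor's computer or in the supervisor's cabinet, where the data are stored. The principal investigator, who is unmasked anyway, could keep it.
2. Have the main supervisor do the data checks and scoring by neutral ID.
3. Keep arm-revealing records, namely the platform-use checklists and discontinuation records, out of the masked dataset.
4. Label the arms A and B for analysis, and open the key only after scoring, imputation and analysis choices are locked.

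The cost is one additional list and, because Stage 3 recruitment began in the first half of 2021, a one-time recode of any records already labelled I or C. Masking cannot be restored for checks already made on those records, but it can apply from then on. No additional staff, visits or participants are needed.

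### The investigator who delivers all in-person sessions also has access to, and helps check, arm-labelled outcome questionnaires

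*Protocol article*

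**What the plan says.** Four parts of the protocol article bear on this.

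- **Delivery (Stage 3, Intervention Procedure).** "The intervention will be performed at Cyprus University of Technology and will be implemented by the principal investigator". There are 12 sessions of 1.5 hours, and no other deliverer is named.
- **Contact outside the sessions (Settings and Sampling).** The principal investigator "will arrange one or two social meetings with the participants of Stage 1 and Stage 3 to achieve some degree of intimacy". For the control group, the same person "will also make a phone call once or twice per month to reassure their participation in the study".
- **Custody, access and checking (Data Management).** "All data will be safely stored in a locked cabinet in the office of the main supervisor", and "The data will also be stored on the computer of the main supervisor". The sentence that begins "Access is granted only to" names two people, the main supervisor and the principal investigator. When the data are put on the computer, these two "will perform a double check to assure that the questionnaires have been completed accurately". Participant codes consist of I or C for the arm, followed by a sequence number.
- **Outcomes (Effectiveness Evaluation).** Quality of life, health locus of control, alcohol use, drug use and drug attitude are scored questionnaires. Bipolar disorder knowledge is a true-false test scored on correct answers. Relapse is counted from hospitalisations.

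**The concern.** The trial is unmasked, and several outcomes rest on what participants say about their drinking, drug use, medication and wellbeing. Such answers are open to social desirability, more so when the person who has taught the participant for weeks can read them. The sessions also teach which answers are the good ones. Under the Stage 3 criteria, stopping medication is a reason for discontinuing participation, and this is stated for the intervention group only. That gives its members a further reason not to show poor adherence to the person running the sessions.

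The second route is the check itself. A judgement on whether a form was completed accurately, made by the person who delivered the intervention and with the arm in view, is not neutral. Both routes would tend to favour the intervention, and the trial has no means of separating them from a real effect.

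**Working it through.** The plan gives no figure on this point, so the main check is to set the roles side by side.

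| Role in Stage 3 | Principal investigator | Main supervisor |
|---|---|---|
| Delivers the in-person sessions | Yes, only person named | Not named |
| Arranges social meetings with participants | Yes | Not named |
| Phones controls | Yes | Not named |
| Keeps the paper and electronic data | No | Yes |
| Has access to the data | Yes | Yes |
| Checks completed questionnaires | Yes | Yes |
| Sees the arm in the code | Yes | Yes |

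The overlap between therapist and unmasked checker is thus written into the text and is not inferred from silence. Neutral codes would not cure it on their own, because the therapist knows which participants attend the sessions.

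**Contact that differs by arm.** Teaching: 12 sessions × 1.5 h = 18 h at most in the intervention arm, none in the control arm during the comparison. The social meetings are for Stage 3 participants, with no restriction to one arm, and controls receive calls once or twice a month. The teaching is therefore clearly arm-specific; the other contact is not.

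**Exposure by outcome.** Most exposed: alcohol use, drug use, drug attitude and quality of life. Less exposed: the knowledge test, where a wish to please does not supply correct answers, and hospitalisation counts and days.

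**Illustration of size.** Inputs from the document: 40 per arm and a .05 significance level (two-sided assumed). Further assumptions: no true effect, no dropout, and a shift of δ SD toward benefit in the intervention arm only. The values of δ (0.1, 0.2, 0.3) are assumed; the documents give none.

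- Degrees of freedom: 40 + 40 − 2 = 78; two-sided 5% critical value of t = 1.991.
- Noncentrality: δ / √(1/40 + 1/40) = δ × √20 = δ × 4.472.
- Chance of a significant result in favour of the intervention: P(T > 1.991), with T noncentral t on 78 df.

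| Assumed shift (SD) | Noncentrality | Chance of false benefit |
|---|---|---|
| 0 | 0 | 0.025 |
| 0.1 | 0.447 | 0.064 |
| 0.2 | 0.894 | 0.141 |
| 0.3 | 1.342 | 0.263 |

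These are rates for one exposed outcome, not for the whole outcome set.

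**The case against.** The strongest reply is that the text establishes less than it suggests at first sight. A reader might infer four things that it does not support.

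- *The therapist holds the data.* This is wrong: paper and files are with the main supervisor, and the principal investigator has access only.
- *Participants hand their answers to the therapist.* The article names the instruments and time points but not who gives out or collects the forms. A condensed article may leave that to the full protocol.
- *The therapist can go back and query answers.* No query process is described. The check is shared by two people and takes place when data are stored, so it may be only a completeness or entry check.
- *Controls have no relationship with this investigator.* The social meetings are not confined to one arm, and the same person phones the controls regularly.

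All four corrections stand, and the concern is limited to access and unmasked checking. It is also true that the error rates measure an assumed bias. They do not show how much of any bias would come from the access rule rather than from participants knowing their arm, which they would in any trial of this kind.

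The reply does not remove the point. Access for the therapist and the therapist's part in the check are stated procedures, and the teaching contact remains specific to one arm.

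**Conclusion.** The point holds in this limited form: the only named therapist is one of two people with access to arm-labelled outcome data and takes part in checking completed questionnaires. Answers on alcohol use, drug use, drug attitude and quality of life are therefore visible to the therapist and checked without masking.

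The likely direction is toward benefit, but the size is unknown. The rates of 6%, 14% and 26% against 2.5% rest entirely on assumed shifts of 0.1, 0.2 and 0.3 SD acting in one arm. They show that a modest shift would matter with 40 per arm, not that one will occur. They should not be applied to the knowledge test or the hospitalisation outcomes. This is a worthwhile and inexpensive improvement in data handling; it does not by itself invalidate the trial.

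**What to change.** Change the Data Management paragraph so that, for Stage 3:

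1. Participants complete the questionnaires without the therapist present and return them sealed.
2. The main supervisor, who already has custody, opens, enters and checks them, with programmed range and completeness checks.
3. The principal investigator has no access to Stage 3 outcome data until the database is locked.
4. Participants are told that the therapist will not see their answers before then.

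Recruitment began in the first semester of 2021, so the change can apply only to forms not yet collected or entered.

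**Cost.** One changed paragraph and no new post, but more data-entry work for the supervisor. There would be no second human checker before lock, and programmed checks replace only part of what a second person does. The principal investigator could no longer follow up incomplete forms. Participants would still know their arm, so response bias would be reduced but not removed.
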